#### Patient medical records and register data

For both women and children in the intervention and control group, we will ask for consent to retrieve relevant information from social and health registries and medical records from pregnancy until the child is 12 months old. This includes attendance at antenatal care visits, pre-gestational BMI, obstetric complications, mode of delivery, birth weight, birth length, APGAR score, number of reportings to social services, EPDS score at child age 2 months, ADBB score at child age 2 months, and height and weight measurements.

#### Administrative data

When the children are 2 years old, we will retrieve data on all families from Danish administrative data such as the Population Statistics Register, the National Patient Register, the National Prescription Register, the National Health Insurance Service Registry, Oral Health Register, the Education Register and the Danish Rational Economic Agents Model (DREAM). With these data, we can examine outcomes such as vaccinations, child examinations at the general practitioner and dentist, use of social and health care services including emergency visits, use of medication, and information about housing, education, and labor market participation for the parents.

For both intervention and CAU families, we will also collect municipal data on what other interventions the family has been offered (including out-of-home care).

We use participants personal identification numbers to retrieve registered data.

#### Fidelity

During the study period, interdisciplinary meetings with the FACAM persons will be held monthly to support uniformity in the care provided to the families. Furthermore, cross-sectorial meetings with participants from the child-and-youth administration, the alcohol and drug treatment, the family clinic, the FACAM persons, the project leaders, and the researchers are held twice a year to support the cross-sectorial collaboration.

We will collect data on the kind of intervention (e.g., method and provider) and the intensity (number and length of sessions) for both intervention and CAU participants. For the intervention group, the FACAM person will answer a short questionnaire after each visit indicating which kind of support they have offered to the family. Participation in the attachment sessions will also be documented.

### Sample size justification

Power analysis (based on an extension of the dependent *t*-test) was carried out in the design phase to assess the statistical power for testing the primary outcome. The power calculation is based on a meta-analysis of interventions aimed to improve parenting sensitivity [87]. The overall average effect size was 0.44 (standardized mean difference (SMD)), but for randomized trials, the average effect size was 0.33. For normally distributed outcomes and using a two-sided alpha of 0.05, and a power of 80%, we would need 160 participants to detect an effect size of 0.44 and 290 participants to detect an effect size of 0.33. We expect around 15% dropout and therefore aim to recruit 330 participants.

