**Methods:**

The study is a prospective randomized controlled trial where we will randomize 320 pregnant women enrolled to receive antenatal care at the family clinic at Odense University Hospital, to either FACAM intervention or usual care. The FACAM intervention consists of extra support by a health nurse or family therapist during pregnancy and until the child starts school. The intervention is most intensive in the first 12 months and also includes attachment-based support provided either individually or in groups. The participants are assessed at baseline, and when the infant is 3 and 12 months old. The primary outcome is maternal sensitivity measured by the Coding Interactive Behavior (CIB) instrument. Secondary outcomes include prenatal parental reflective functioning, mental well-being, depressive symptoms, breastfeeding duration, maternal satisfaction, child development, parent competence, parental stress, and activities with the child.

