## Methods and design

The study is a prospective, superiority, parallel, 1:1 randomized controlled trial with two study arms: intervention (FACAM) and care as usual (CAU). Pregnant women are randomized to receive either FACAM or CAU. Participants will receive oral and written information on the project and will give written consent to participate in the trial. For participants below 18 consent will also be collected from a parent or guardian. Ethical approval has been obtained from the internal review board at VIVE. The Committee on Health Research Ethics in the Region of Southern Denmark has assessed the protocol and found no need for further approval of the study (Case no. S-20182000-110). The study has obtained approval from the committee of Health Research in the Region of Southern Denmark (journal no. 18/48509). The protocol conforms to the Standard Protocol Items: Recommendations for Interventional Trials (SPIRIT) guidelines (Fig. 1). The final reports of the trial will be written following the Consolidated Standards of Reporting Trials (CONSORT) statement.

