### Procedures and randomization

We will recruit 320 pregnant women—160 to FACAM and 160 to CAU. The flow chart is presented in Fig. 2.

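### The recruitment target is given as both 330 and 320, and neither follows from 290 analysable women and 15% dropout, which need 342; the stated 80% power is missed by about 1 to 3 points

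*Protocol article*

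**What the plan says.** The protocol article's section on sample size justification takes two effect sizes from a meta-analysis of interventions on parenting sensitivity: an overall average of 0.44, "but for randomized trials, the average effect size was 0.33". It treats the outcome as normal, sets a two-sided 5% significance level and 80% power, and states that "we would need 160 participants to detect an effect size of 0.44 and 290 participants to detect an effect size of 0.33". It closes with: "We expect around 15% dropout and therefore aim to recruit 330 participants". The section describes the calculation as an extension of the dependent t-test.

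Elsewhere the target is different. The section on procedures and randomization says: "We will recruit 320 pregnant women—160 to FACAM and 160 to CAU". The abstract says "we will randomize 320 pregnant women". The Discussion reports that, at planning, about 160 women were expected in each of the two concern groups, which again sums to 320.

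The design section describes a "prospective, superiority, parallel, 1:1 randomized controlled trial with two study arms". The data analysis section compares group means by linear regression.

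**The concern.** Two things do not fit together. First, the number to recruit is 330 in the only section that justifies it and 320 in the abstract and the procedures section. Both the sample size section and the procedures section speak of recruiting, so these are not an enrolled and an analysed count. Second, the sample size section presents 330 as the consequence of 290 analysable women and about 15% dropout, and it is not.

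Readers will use the target to judge whether the trial completed recruitment, and the power statement to judge a null result on maternal sensitivity. With 320 women enrolled, the trial would be complete by the procedures section and ten short by the sample size section. In addition, neither figure gives the stated 80% power at the plan's own dropout rate.

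**Working it through.** **Inputs.** From the sample size section: two-sided alpha 0.05, power 80%, SMD 0.33 (so SD = 1), 290 analysable, dropout about 15%, target 330. From the abstract and the procedures section: target 320. From the design section: two parallel arms, 1:1.

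**Step 1: reproduce the plan's 290.** For two independent means, n per arm = 2 × (1.960 + 0.842)² / 0.33² = 2 × 7.849 / 0.1089 = 144.2, rounded up to 145, so 290 in total. Power at 145 per arm is 80.2% by the normal approximation and 79.97% by the noncentral t. The stated 290 therefore reproduces, and it does so with the independent two-sample formula.

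**Step 2: inflate for dropout.** Recruits = analysable / (1 − dropout) = 290 / 0.85 = 341.2, so 342 (171 per arm). The target of 330 is 12 short of this and 320 is 22 short. The common shortcut of multiplying by 1.15 gives 333.5. That is close to 330 and may be where it came from, but the article does not say. Neither route gives 320.

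**Step 3: dropout that each target can absorb and still leave 290.**
- 330: 1 − 290/330 = 12.1%
- 320: 1 − 290/320 = 9.4%

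**Step 4: power at SMD 0.33 with 15% dropout.** The normal approximation is Φ(0.33 × √(n/2) − 1.960), with n analysed per arm. The t-test column uses the noncentral t.

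| Recruited | Analysed (× 0.85) | Power, normal | Power, t-test | SMD with 80% power (t-test) |
|---|---|---|---|---|
| 320 | 272 | 77.7% | 77.4% | 0.341 |
| 330 | 280.5 | 78.9% | 78.6% | 0.336 |
| 342 | 290.7 | 80.3% | 80.1% | 0.330 |

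For example, with 320 recruits n = 136 per arm: 0.33 × √68 = 2.721; 2.721 − 1.960 = 0.761; Φ(0.761) = 77.7%.

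**Step 5: sensitivity to the dropout figure, which the plan gives only as approximate (t-test, SMD 0.33).**

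| Dropout | 320 recruited | 330 recruited |
|---|---|---|
| 10% | 79.7% | 80.9% |
| 12% | 78.8% | 80.0% |
| 15% | 77.4% | 78.6% |
| 20% | 74.9% | 76.1% |

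At SMD 0.44, 272 analysed women give about 95% power, and 280 about 96%.

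**The case against.** The strongest reply is that this hardly matters. The loss at 15% dropout is 1.4 points for 330 and 2.6 points for 320, and the detectable SMD moves from 0.33 to 0.336 or 0.341. Dropout is given only as approximate, and 330 still works at 12%. At the plan's other effect size the power is about 95% with either target. No estimand, design feature or analysis changes. All of this stands, and it limits the severity. It does not remove the two conflicting targets or make 330 the result of the stated inputs, and 320 needs dropout below 10%.

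It could also be said that multiple imputation keeps every randomised woman in the primary analysis. The sample size section nevertheless inflates for dropout, so it counts dropouts as lost information, and the article never offers imputation as grounds for a smaller target. Nor does condensation into an article explain the problem, because the article prints both figures itself.

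A reader might infer more than the document supports:
- **That the trial is materially underpowered and must recruit more.** The shortfall is too small for that.
- **That 320 is the true target, or that the target was lowered during the trial.** Several places say 320, but the only justification says 330, and the article does not record which was pre-specified or whether it changed.
- **That 290 is wrong because a dependent t-test is named.** The 290 matches the independent two-sample formula. What a paired calculation would give depends on a within-pair correlation that is not stated, and the extension is not described. The label needs reconciling; the 290 does not.
- **That the 160 quoted for SMD 0.44 is a further error.** The normal formula gives 164, and 160 gives 79.0% power. The difference is under 3%, and the trial was not sized on it.

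**Conclusion.** The point holds as a should-fix. The recruitment target has two unreconciled values, 330 and 320, and neither equals the 342 that 290 analysable women and 15% dropout require. At SMD 0.33 the power is 78.6% for 330 and 77.4% for 320, so the stated 80% is missed by about 1 to 3 points.

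These powers assume two equal independent groups, a normally distributed outcome, two-sided alpha 0.05, no gain from covariate adjustment or imputation, and dropout of exactly 15%, equal in both arms. The contradiction between 320 and 330 rests on none of these. The Discussion reports poorer retention among women with a high level of concern, so overall dropout could differ from the planning value in either direction depending on the final mix; the second table in the working shows how power moves with it.

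**What to change.** - Have the investigators confirm which target was pre-specified, use it in the abstract, the procedures section and the sample size section, and explain in a sentence how the other figure arose. The review should not choose between them.
- Restate the power for the confirmed target, for example: with 330 randomised and 15% dropout, about 280 women contribute to the 12-month primary outcome, giving about 79% power at SMD 0.33 (80% at SMD 0.336), two-sided alpha 0.05. For 320 the figures are 272 women, about 77% power and SMD 0.341.
- Reconcile the reference to the dependent t-test with the parallel two-arm design. If the independent two-sample calculation was used, as the 290 suggests, name it; if not, describe the extension and give its inputs.

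The cost is wording only: no added recruitment, burden or delay. The stated power becomes slightly less favourable.

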### Data analysis

The primary outcome (CIB parental sensitivity at 12 months) is tested using linear regression with robust standard errors since we are interested in the mean difference between the groups but do not expect a perfectly normal distribution of data. The treatment effect is estimated as a fixed effect using a binary indicator of treatment. A Wilcoxon rank-sum test will be used in the case of severe non-normality. Variables with indications (*p* < 0.1) of the differences between intervention and CAU groups at baseline are used as control variables. Missing data is handled using multiple imputations using all available baseline data. Secondary outcomes are analyzed following the same principles.

Additional exploratory analyses will be carried out in a mixed-effects regression framework. This allows for growth curve estimation. Two-sided tests with 0.05 significance levels are applied throughout.

In addition to the primary analysis, we will perform subgroup analyses to examine the potential differences between subsets of participants. Hence, we analyze the subgroups according to the following characteristics: primiparous or multiparous, education (high school or less versus more than high school), concern about the family (level 1/2 or level 3/4), provider (health visitor or family therapist), adult attachment style (ECR-S), initial trauma level (ACE < 3 or ACE ≥ 3), the initial level of reflective function (lowest 50% versus highest 50%), the initial level of depression or anxiety (clinical or not-clinical level), and attendance (dose).

The primary analysis will be based on the intention-to-treat (ITT) principle, aiming to include all participants in the arm they were originally allocated to irrespective of the amount of treatment received. Missing data is handled using multiple imputations using all available baseline data. Sensitivity analyses will be performed to investigate the potential impact of missing data, in particular, by using a pre-specified conservative multiple imputation strategy and a complete case analysis.

We do not expect that participants will be harmed by the study and therefore have no predefined stopping guidelines and no a priori planned interim analyses.

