#### Primary outcome

The primary outcome is maternal sensitivity measured by the Coding Interactive Behavior (CIB) instrument [67] at child age 12 months. The main hypothesis is that mothers in the intervention group will have a higher level of parental sensitivity (a CIB composite) than mothers in the control group. Maternal sensitivity is a subscale of the CIB. The CIB is a global rating system for social interactions that includes 22 parent codes, 16 child codes, and 5 dyadic codes rated on a scale of 1 to 5 which can be aggregated into the following composites: sensitivity, intrusiveness, limit setting, involvement, withdrawal, compliance, dyadic reciprocity, and dyadic negative states. The CIB is coded based on a 6-min mother-infant free play interaction recorded in the home or at another location if preferred by the family. The CIB system has been validated as an assessment measure in multiple studies of mother-child interactions in both normative and high-risk populations and shows stability over time, predictive validity, and adequate psychometric properties [67–71]. Mother-infant interactions are coded by reliable coders blind to treatment allocation. The inter-coder agreement will be calculated on a 10% randomly selected subset of the sample.

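### The distribution-triggered switch to a Wilcoxon rank-sum test replaces the declared mean-difference target and does not fit the plan's own adjustment and imputation

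*Protocol article*

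**What the plan says.** All of this is in the Data analysis section of the protocol article unless noted.

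- **Target and method.** The primary outcome is analysed by "linear regression with robust standard errors since we are interested in the mean difference between the groups but do not expect a perfectly normal distribution". Non-normality is thus already part of the reason for the method.
- **Switch.** Shortly afterwards: "A Wilcoxon rank-sum test will be used in the case of severe non-normality". It is worded as what will be done. It is not among the sensitivity analyses, which the section names separately and which concern missing data only.
- **Adjustment.** Variables with indications (p < 0.1) "of the differences between intervention and CAU groups at baseline are used as control variables".
- **Missing data.** "Missing data is handled using multiple imputations using all available baseline data".
- **Reach.** Secondary outcomes follow the same principles. "Two-sided tests with 0.05 significance levels are applied throughout".
- **Outcome scale.** Under Primary outcome, the CIB codes are "rated on a scale of 1 to 5 which can be aggregated into the following composites"; sensitivity is one of these composites.

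**The concern.** The paragraph gives two answers to one question. Its first sentence settles non-normality with a method that targets the mean difference and does not need normal data. The switch then treats a stronger degree of the same condition as grounds for a different test.

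The rank-sum test does not test the mean difference under weaker assumptions. It tests whether P(Y1 > Y0) departs from one half, and it agrees with a test of means only under extra conditions, such as a pure shift between arms of the same shape. Those conditions are not assured here. The intervention is tailored to each woman, and provider and attachment course differ by level of concern, so a change in spread as well as in level is plausible.

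Three things are at stake:

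- The hypothesis tested for the primary outcome would depend on the data.
- If the switch operates, the sentences on control variables and multiple imputation no longer fit the test in its plain form.
- Among the secondary outcomes, some could be reported as adjusted mean differences and others as unadjusted rank tests. Several are short bounded scores, such as the two Parenting Stress Scale subscales (0–9 and 0–7), for which severe non-normality is easy to imagine.

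**Working it through.** **1. The plan's own sample size, to see which scale it is built on.** Inputs from Sample size justification: SMD 0.33, "using a two-sided alpha of 0.05, and a power of 80" percent, 1:1 allocation.

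n per arm = 2 × (1.960 + 0.842)² / 0.33² = 2 × 7.85 / 0.1089 ≈ 144.2, rounded up to 145, so 290 in total. This matches the stated 290. The trial is therefore sized for a comparison of means.

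**2. Numbers analysed.** With 320 recruited (Procedures and randomization) and 15% dropout: 320 × 0.85 / 2 = 136 per arm. The Sample size justification says 330, which gives 330 × 0.85 / 2 ≈ 140. The smaller figure is used below.

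**3. Does the robust mean test need a fallback?** Simulation: 20,000 trials per scenario, 136 per arm, both arms drawn from the same skewed distribution. Two shapes were bounded at 1–5, written as 1 + 4 × Beta(a, b), and one was a reflected lognormal. The mean test was the unequal-variance comparison, which is what robust regression on a binary indicator amounts to without covariates. The shapes and the trigger (absolute residual skewness above 1) are assumptions, because the article gives neither. So is treating the composite as staying on the 1–5 scale of its codes.

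| Identical arms | Mean test | Wilcoxon | Switch rule |
|---|---|---|---|
| Beta(5, 1.2) | 5.1% | 5.2% | 5.5% |
| Beta(6, 0.7) | 5.0% | 5.1% | 5.1% |
| Reflected lognormal | 4.7% | 5.0% | 5.0% |

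The mean test holds its level in all three, so the fallback is not needed for validity.

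**4. Does the switch change the question?** Equal means, unequal spread, outcome bounded at 1–5. For Beta with mean m and concentration k, the outcome mean is 1 + 4m and its SD is 4 × √(m(1 − m)/(k + 1)).

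- Scenario A: m = 0.80, k = 3 against 12. Both means are 4.2. The SDs are 4 × √(0.16/4) = 0.80 and 4 × √(0.16/13) ≈ 0.44.
- Scenario B: m = 0.85, k = 3 against 8. Both means are 4.4. The SDs are 4 × √(0.1275/4) ≈ 0.71 and 4 × √(0.1275/9) ≈ 0.48.

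| Equal means | Mean test rejects | Wilcoxon rejects | Trigger fires | Switch rule rejects |
|---|---|---|---|---|
| A | 5.2% | 62.8% | 91% | 61.4% |
| B | 5.2% | 66.0% | >99% | 66.0% |

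A further set of assumed skewed shapes gave 51–72% for Wilcoxon and the switch rule, again against about 5% for the mean test. These rejections are not errors of the rank-sum test on its own terms, since the distributions do differ. They are errors if read as evidence on the mean difference.

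**5. Fit with the rest of the paragraph.** A plain rank-sum test has no place for control variables. It yields no adjusted difference on the CIB scale and no estimate with a standard error to combine over imputed data sets in the usual way. The article does not say how these would be reconciled.

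**The case against.** Several points on the other side are sound.

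- **The trigger.** What counts as severe, by which diagnostic and when, is commonly left to an analysis plan or full protocol, and neither is shown. That stands, so the missing definition is not the point. A definition would still leave the change of target and the clash with adjustment and imputation.
- **Power.** A reader might infer that the switch costs power, for example from 85% to 80% through lost adjustment. The documents do not support this. The 85% assumes pre-specified covariates with R² of 0.20, a figure the article does not give, and Table 1 shows no baseline CIB score. The plan adjusts only for variables that differ at p < 0.1. Simulated with that same assumed R², this rule added only about 1 to 2 percentage points over no adjustment. Under a pure shift in skewed data the rank-sum test had more power, 87–98% against 77–78% depending on the assumed shape. That is a real advantage of the rank test.
- **False positives.** A reader might infer a materially inflated type I error. With identical arms and a mechanical rule it was 5.0–5.5%. It reached 6.7–7.5% only with free choice of the smaller p-value. The article does not provide for that, and its blinding of data analysts makes it less likely.
- **ITT and the stratum.** A reader might say the switch breaks intention to treat or loses the randomisation stratum. It does neither: women are still analysed in their allocated arm, and the stratum is not in the specified regression. Stratified rank tests and ways of pooling rank statistics exist, though they are less routine and not what is written.
- **Reach.** For a bounded composite the clause may never operate for the primary outcome, and it does not say that the mean-difference estimate would be withdrawn. Both are fair. They limit the consequence but do not remove the inconsistency, and the clause also covers the secondary outcomes.

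**Conclusion.** The concern holds as a matter of the target. The plan states an interest in the mean difference, picks a method suited to it without normality, and then lets the observed distribution substitute a test of something else. That test, as named, cannot carry the adjustment and does not combine routinely with the imputation.

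The size depends on how the arms differ. With identical arms there is almost no effect on type I error. With a pure skewed shift the rank test gains power. With equal means and unequal spread, about 50–70% of trials in the assumed scenarios would give a significant primary result with no difference in means, against about 5% for the robust mean test. These figures rest on assumed outcome shapes, 136 per arm and, for the switch rule, an assumed trigger. They show that the discrepancy can be large, not that it will be. It is worth correcting before the analysis and is no threat to the trial's design.

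**What to change.** Delete the switch sentence and state that linear regression with robust standard errors is the primary analysis whatever the distribution of the outcome, for the primary and secondary outcomes alike. If a check against skewness is wanted, name one pre-specified sensitivity analysis that does not replace the primary result. A bootstrap confidence interval for the adjusted mean difference, or a proportional-odds model, would keep the covariates and the imputed data. A rank-sum test could serve as a descriptive supplement.

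The cost is one sentence, with no change in sample size and no new data. The price is giving up the rank test's possible power advantage if the outcome is severely skewed and the effect is a pure shift. The change can be reported under the article's own provision for protocol amendments.

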When a mother has consented to participate, a research team member registers the participant and sends out the baseline questionnaire. When the participant has filled out the baseline questionnaire, the participant is randomized by a research team member to receive either FACAM or CAU (1:1). The randomization is conducted with the tool “OPEN randomize” in REDCap and the procedure is logged. The randomization sequence was generated by an independent data analyst before recruitment started. Participants are stratified into two groups according to the level of concern assessed by the healthcare professionals which is filled out when participants are invited to participate in the study (levels 1 and 2 are categorized as a high concern, and levels 3 and 4 are categorized as a low concern). When the participant is randomized, the researcher informs the participant and the project coordinator at the municipality about which group the participant is allocated to. The project coordinator at Odense municipality then allocates a FACAM-person to the intervention families prioritizing FAMKO persons with free capacity in the same geographical area. If a group of FAMKO persons with free capacity is under a lot of pressure due to, e.g., sickness, the coordinator will then usually allocate a FAMKO person from another group. After the FAMKO person is allocated, the intervention commences.

The consent form and other related documentation are given to participants are available from the authors on request. The study has no trial steering committee or data monitoring committee as this is not required for behavioral interventions [59, 60].

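### Choosing covariates by baseline tests at p < 0.1, with no term named for the randomisation stratum, makes the analysis conservative and forgoes power that a pre-specified model would give

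*Protocol article*

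**What the plan says.** Under Data analysis, the primary outcome (CIB sensitivity at 12 months) is tested by linear regression with robust standard errors on a binary treatment indicator. Covariates come from one rule: variables with p < 0.1 in tests "of the differences between intervention and CAU groups at baseline are used as control variables". It extends to the other endpoints: "Secondary outcomes are analyzed following the same principles".

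Under Procedures and randomization: "Participants are stratified into two groups according to the level of concern assessed by the healthcare professionals" (levels 1 and 2 against levels 3 and 4). In Data analysis, level of concern appears only among the subgroup factors.

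The sample size section states that the trial needs "290 participants to detect an effect size of 0.33", and then: "We expect around 15% dropout and therefore aim to recruit 330 participants". The Procedures section gives the target as 320.

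**The concern.** For a variable measured before randomisation, a between-arm difference at p < 0.1 is a chance event. It says nothing about whether the variable predicts maternal sensitivity. Three things follow.

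- The primary model cannot be written down until between-arm baseline data have been examined, and the candidate variables are not listed.
- The rule works against the stratifier. Stratification balances level of concern, so it should not show a difference, yet the protocol itself ties levels 1 and 2 to a risk of inadequate parenting, which is close to what the primary outcome measures.
- The T0 value of a secondary outcome enters its model only if it happens to be imbalanced: WEMWBS for later WEMWBS, HADS as a proxy for EPDS.

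At stake are the precision and calibration of the primary test, in a trial whose planned size leaves no spare power.

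**Working it through.** **1. The plan's own figures.** Per arm, n = 2(1.96 + 0.8416)² / SMD².
- SMD 0.33: 15.70 / 0.1089 = 144.2, so 145 per arm and 290 in total, as stated.
- SMD 0.44: 15.70 / 0.1936 = 81.1, so 82 per arm and 164 in total, against 160 stated.

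These are unadjusted two-group calculations; no covariate gain is counted. With 15% dropout, 330 × 0.85 = 280.5 and 320 × 0.85 = 272. Unadjusted power is Φ(0.33·√N/2 − 1.96), which is 0.789 and 0.777.

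**2. Selection by chance.** With k independent candidates, P(at least one selected) = 1 − 0.9^k.
- k = 10: 0.65
- k = 15: 0.79
- k = 25: 0.93

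The expected number selected is 0.1k: 1.0, 1.5 and 2.5. The protocol does not fix k, and correlation between candidates would lower these probabilities.

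**3. The stratum.** Assume permuted blocks of 4 within strata (block size is not stated). The imbalance is then at most 2 women per stratum. Take 280 women, one third of them high concern (the Discussion expects 2/3 low concern). The worst case is 47/140 against 45/140, a difference of 0.0143. Its standard error is √(2 × (1/3)(2/3)/140) = 0.056, so z is about 0.25, far from the 1.645 needed for p < 0.1. In simulation the stratum was selected in 0 of 8,000 replicates in every scenario.

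**4. Why the standard error is too large.** Leaving out a balanced stratifier overstates the standard error by about 1/√(1 − R²). Type I error is then 2[1 − Φ(1.96/√(1 − R²))], which is 0.044 at R² 0.05 and 0.039 at R² 0.10. Selecting on imbalance adds to this. Covariates are left out exactly when they are balanced, so their variance stays in the reported error although it contributes little to the actual error.

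**5. Size.** Simulation: 280 analysed, SMD 0.33, strata 1/3 and 2/3, blocks of 4, 15 candidates of which 3 are prognostic, HC1 standard errors, 8,000 replicates. All R² values are assumptions. SE ratio is mean estimated SE over empirical SD. Pre-specified means arm, stratum and the prognostic covariates.

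| R² stratum + covariates | Rule: type I | Rule: SE ratio | Rule: power | Pre-specified: type I | Pre-specified: power |
|---|---|---|---|---|---|
| 0 + 0 | 0.049 | 1.00 | 0.77 | 0.047 | 0.78 |
| 0.05 + 0.10 | 0.042 | 1.03–1.04 | 0.79 | 0.050 | 0.85 |
| 0.10 + 0.20 | 0.034 | 1.08–1.09 | 0.81 | 0.050 | 0.91 |

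Monte Carlo error is about √(0.05 × 0.95/8000) = 0.0024 for type I error and 0.0045 for power near 0.8. A separate simulation gave, rule against pre-specified, power of 0.785 vs 0.787, 0.81 vs 0.84 and 0.80 vs 0.90, with type I error under the rule of 0.039 and 0.031 in the last two rows.

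Keeping the rule but forcing the stratum into the model gives power of 0.77, 0.81 and 0.84, which recovers only part of the gain. With no covariates at all, power is 0.78, 0.79 and 0.80, so the rule does about as well as no adjustment.

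**6. Ordinary covariates.** With 272 analysed, four unstratified covariates and total R² 0.20 (6,000 replicates), the unadjusted test had type I error 5.0% and power 76.6%. The rule gave 4.2% and 78.4%. Pre-specified adjustment gave 85.0% power.

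**7. Timing.** Randomisation follows completion of the baseline questionnaire (Procedures and randomization). The second baseline part, with P-PRFQ, ACE and PTSD-8, is at gestational week 25 (Data collection; Table 1). Those values may post-date allocation, and the rule as written could then adjust for a post-randomisation difference.

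**The case against.** The strongest reply is that the rule is stated in advance, looks at baseline data and not at outcomes, and is applied by analysts who are blinded to allocation. It errs on the safe side, and a condensed article may leave the stratum term to the analysis plan. The documents give no evidence on how well level of concern or any baseline measure predicts CIB sensitivity. If nothing is prognostic, the cost is about one percentage point of power or less.

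Much of this stands, and it rules out four stronger readings that a reader might infer.

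- That the rule inflates false positives. It does not: type I error is at or below 0.05 in every scenario.
- That leaving out any prognostic covariate invalidates the test. Step 6 shows otherwise; miscalibration comes from omitting a balanced stratifier and from selecting on imbalance.
- That the rule pushes power below 80%. Against the unadjusted calculation in the protocol it loses essentially nothing. The shortfall comes from the recruitment target (290/0.85 = 341.2, so 342 would be needed), which is a separate matter.
- That the protocol excludes the stratum. It only fails to name it, and its near-certain non-selection depends on blocking that the text does not describe.

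What the reply does not remove is the rule itself. It is written into the protocol, and an analysis plan consistent with the protocol would carry it forward.

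**Conclusion.** The point holds as a should-fix matter. The stated rule performs worse than a simple alternative that uses data already collected, and it leaves the primary model undetermined until baseline imbalances are seen.

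The harm is lost efficiency and a conservative test, not bias towards a positive result. On the assumptions above, the forgone power runs from about nothing (R² 0) through 3 to 6 points (total R² 0.15) to about 10 points (total R² 0.30). Robust standard errors do not cure the conservatism, since the simulations already use them. The range rests on assumed R² values, about 280 analysed and blocking within strata.

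**What to change.** Delete the p < 0.1 rule and drop between-arm significance tests as a basis for adjustment. Fix the primary model as CIB sensitivity at 12 months on arm, level-of-concern stratum (1/2 vs 3/4) and a short list of covariates measured before randomisation, with robust standard errors. The trial team should choose the list in advance for expected prognostic value; the documents do not show which variables qualify.

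For each secondary outcome, add its own T0 value or nearest T0 proxy where one was collected (WEMWBS for WEMWBS, HADS for EPDS). As an illustration, an assumed baseline correlation of 0.5 would cut residual variance by 0.5² = 25%.

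Do not adjust for the week-25 measures (P-PRFQ, ACE, PTSD-8) where they may follow allocation.

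Cost: no new data, because level of concern is recorded at invitation and women complete the T0 questionnaire before they are randomised. Recruitment began in October 2018, so this is a mid-trial amendment. It should be dated before unblinding and reported as the Protocol amendments section provides.
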